## 2 Background information

### 2.1 Irritable bowel syndrome

Irritable bowel syndrome (IBS) is a very common disorder with a worldwide prevalence of 10-20%. Even though it is not life-threatening or associated with higher mortality, it profoundly affects the patients' quality of life and causes substantial economic costs due to the need for medical consultation and work absenteeism (Sandler et al. 2002).

Symptoms vary between patients and include constipation and/or diarrhoea, abdominal pain and cramps, flatulence, faecal urgency, a sense of incomplete evacuation and relief of pain or discomfort upon defaecation. IBS is classified according to the Rome IV criteria as recurrent abdominal pain, on average, at least 1 day/week in the last 3 months associated with 2 or more of the following: Related to defaecation, associated with a change in frequency of stool, or associated with a change in form (appearance) of stool (Lacy 2015). IBS subtypes can further be classified according to predominant stool patterns: IBS with constipation (IBS-C), IBS with diarrhoea (IBS-D), and IBS with alternating symptoms of diarrhoea and constipation (IBS-M), and unsubtyped IBS (Longstreth et al. 2006).

Even though the aetiology and pathophysiology of IBS are complex and not well understood, it is well accepted that a dysregulation of the microbe-gut-brain axis plays an important role. Associated aberrations include visceral hypersensitivity, abnormal gut motility, gut microbiota changes and autonomic nervous system dysfunction (Mayer et al. 2015). In addition, there is a growing amount of data revealing a contributing role of an aberrant immune system in the pathogenesis of IBS. Mild immune activation has been found both locally in the gut and systemically (Barbara et al. 2011; Sundin et al. 2014). Furthermore, psychological and environmental factors like anxiety, depression and significant negative life events are believed to contribute to IBS development (Mayer et al. 2015).

Diagnosis of IBS is mainly based on symptomatology and absence of clear organic diseases, rather than on pathophysiologic mechanisms. There are no preventive strategies and current therapy is not firmly based on sound physiologic principles but mainly aims at alleviating symptoms of abdominal pain or altered bowel transit. The efficacy of current treatment is limited and new therapies are needed.

### 2.2 Intestinal permeability in IBS

The intestinal barrier is an important component in the interplay between the gut and the brain. It prevents translocation of harmful substances and pathogens from the external environment while allowing a peaceful coexistence with intestinal symbionts without causing chronic inflammation (König et al. 2016). The physical barrier is mainly formed by the mucus layer, the epithelial layer and the underlying lamina propria. Tight junction proteins connect the intestinal epithelial cells and regulate paracellular permeability. The functional barrier includes components such as immune cells, the intestinal microbiota and antimicrobial peptides, which play crucial roles in supporting appropriate gut barrier function. Disruption of this barrier results in increased intestinal permeability, which in turn facilitates translocation of harmful

substances and pathogens to the bloodstream (König et al. 2016). An increased intestinal permeability has been related to several diseases such as inflammatory bowel diseases, coeliac disease, obesity, and also irritable bowel syndrome (IBS) (König et al. 2016). Studies using *in vivo* methods have shown that about 40% of IBS patients, and mostly those with diarrhoea as their main symptom, have signs of increased intestinal permeability (Dunlop et al. 2006) (Zhou, Zhang, and Verne 2009) (Zhou et al. 2010) (Gecse et al. 2012) (Mujagic et al. 2014). *Ex vivo* experiments showed that colon biopsies of IBS patients display an increased permeability and release soluble factors that can reduce barrier function in other cells (Piche et al. 2009) (Han et al. 2012). Also psychological stress, which is often increased in IBS patients, is known to enhance intestinal permeability via the hypothalamic-pituitary-adrenal (HPA) axis and mast cell activation (Vanuytsel et al. 2014).

### 2.3 Assessment of intestinal barrier function

The permeability of the small intestine is commonly evaluated by measurement of the intestinal permeation and urinary excretion of orally administered water-soluble, non-fermentable sugars that differ in size. The larger sugar molecules, such as lactulose, can only cross the intestinal barrier by paracellular passage, and are not taken up actively. The smaller molecules, such as rhamnose, cross the epithelial barrier transcellularly and act as a control for gastric emptying, dilution, transit time, and epithelial absorptive area, as well as systemic distribution and renal function. The urinary excretion ratio is then used as a standardised assessment of the intestinal permeability of the intestinal segment where the permeability probes are absorbed (König et al. 2016; van Wijck et al. 2013).

Other potential biomarkers of epithelial integrity, which have a causal relationship with permeability and innate barrier function, are molecules produced by epithelial cells. Serum levels of tight junction proteins such as zonulin are promising biomarkers of epithelial integrity (Wells et al. 2017). Zonulin can also be detected in faecal samples.

Additional sensitive biomarkers for detection of tissue injury are fatty acid-binding proteins (FABP), which are tissue-specific, small cytosolic proteins (Pelsers, Hermens, and Glatz 2005). Intestinal FABP (i-FABP) is particularly highly expressed in cells present on the tips of the villi and not in the crypt (Pelsers et al. 2003). As the villi is the initial site of destruction, upon epithelial damage i-FABP proteins are released into the systemic circulation, and have therefore been reported as useful markers to detect early stages of epithelial cell damage (Wells et al. 2017). i-FABP can be measured in plasma using enzyme-linked immunosorbent assays (ELISAs) (Wells et al. 2017).

An increase in intestinal permeability potentially leads to translocation of microbiota or their toxic products. A promising markers reflecting translocation of bacteria or their products into the circulation is bacterial 16S ribosomal RNA (rRNA).

The cortisol awakening rhythm is a robust marker of stress and has been assessed in several clinical disorders, including IBS. For example, Suárez-Hitz et al. found that IBS patients with predominant diarrhea exhibited substantially heightened cortisol levels at awakening and a

blunted cortisol awakening response (Suarez-Hitz et al. 2012).

## 2.4 Probiotic intervention studies

Several meta-analyses have shown that the intake of specific beneficial bacteria, so-called probiotics, can improve gastrointestinal symptoms of IBS patients (Moayyedi et al. 2010; Ford et al. 2014). In addition, there is evidence that administration of probiotics and prebiotics can positively affect stress levels (Pinto-Sanchez et al. 2017) (Takada et al. 2016) (Schmidt et al. 2015). The mechanisms behind the beneficial effect of probiotics are still mostly unknown. A possible mechanism could be a strengthening of the barrier function. A study by principal investigator [name] showed that a probiotic administered by a feeding tube could strengthen the intestinal barrier both in healthy volunteers as well as IBS patients (Karczewski et al. 2010). Both strains in the probiotic products used in the current study have shown to reduce intestinal permeability in pre-clinical studies (Karimi et al. 2018).

## 3 Study objectives

**The overarching aim** of this study is to investigate the effect of a 6-week intervention with two different probiotic products ((*Lactobacillus reuteri* ATCC PTA 6475 och Gastrus (*Lactobacillus reuteri* DSM 17938/ATCC PTA 6475)) on the intestinal permeability of diarrhoea-predominant IBS (IBS-D) patients.

**The primary endpoint** is the difference in small intestinal permeability, measured as the urinary lactulose/rhamnose secretion ratio, after a 6-week intervention with the probiotic products compared to the placebo product, in IBS-D patients.

**Secondary endpoints** are the differences between intervention with the probiotic products compared to the placebo in IBS-D patients on:

- The small intestinal permeability, measured as the urinary lactulose/rhamnose secretion ratio, after 3-week intervention
- Whole gut permeability measured as urinary sucralose/erythritol excretion ratio (0-24hrs) after 3 and 6 weeks
- Colonic permeability measured as urinary sucralose/erythritol ratio (5-24hrs) after 3 and 6 weeks
- Gastroduodenal permeability measured as urinary sucrose excretion (0-5hrs) after 3 and 6 weeks
- Various potential biomarkers of general intestinal barrier function and inflammation in blood and faecal samples after 3 and 6 weeks such as plasma i-FABP, faecal zonulin, serum zonulin, bacterial 16S ribosomal RNA (16S rRNA) gene copy number (whole blood), plasma vasoactive intestinal polypeptide (VIP), plasma high-sensitive C-reactive protein (hs-CRP), faecal calprotectin and plasma cytokines (e.g. IL-6 and IL-10)

**Exploratory endpoints** are the effects of the intervention with the probiotic products in comparison to the placebo in IBS-D patients on:

- Stool frequency and consistency (Daily diary on bowel movement using Bristol Stool Chart)
- Gastrointestinal symptoms as measured by the GSRS-IBS and IBS-SSS after 3 and 6 weeks
- Quality of life after 3 and 6 weeks (5Q-5D-5L, IBS-QOL)
- Perceived stress after 6 weeks (using the Perceived stress scale, PSS)
- Anxiety and depression symptoms after 3 and 6 weeks (HADS)
- Cortisol awakening rhythm (saliva) after 3 and 6 weeks
- Intestinal microbiota composition (16S rRNA-based next generation sequencing of faecal samples) after 3 and 6 weeks
- Metabolomic profile of faecal samples and blood, including SCFA metabolism and tryptophan catabolites such as 5-HT and melatonin, after 3 and 6 weeks.

#### 4 Study design

This will be a single-centre, randomised, double-blinded, placebo-controlled intervention study with a parallel design and three study arms.

The study will investigate the effects of supplementation with the probiotic products *L. reuteri* ATCC PTA 6475 and Gastrus (*L. reuteri* DSM 17938/ATCC PTA 6475) on the intestinal barrier function, gut health and stress symptoms in diarrhoea-predominant IBS (IBS-D) patients. The test product is a tablet containing either ATCC PTA 6475 or Gastrus (DSM 17938/ATCC PTA 6475). The subjects will consume the product twice a day, giving a daily dose of  $1 \times 10^9$  CFU of each strain. The placebo product is an identical tablet except for the absence of probiotics. After having given their written informed consent, subjects will complete screening procedures to evaluate their eligibility for the study (visit 1). Study participants will undergo two baseline visits (visits 2 and 3, 3 weeks apart) to account for individual variations, and will then be randomly assigned to 6-week intake of either ATCC PTA 6475, Gastrus, or placebo in a ratio of 1:1:1 (stratified by sex). Participants will attend a study visit three weeks into the intervention (visit 4) and at the end of the intervention (visit 5, week 6). The intestinal permeability will be assessed using a standardized multi-sugar test at visit 2, visit 3, visit 4, and at end of intervention (visit 5). Blood, saliva and faecal samples will be collected at visit 2-5. In addition, gastrointestinal symptoms will be recorded at those visits (using GSRS-IBS, IBS-SSS). Quality of life using the 5Q-5D-5L and Hospital Anxiety and Depression Scale (HADS) scores will also be recorded at those visits. In addition, at visit 3 and visit 5, the IBS-QoL and the Perceived Stress Scale (PSS) will be completed. In a daily diary, participants will record stool frequency and consistency from visit 2 until end-of-study visit 5. Dietary habits of the patients will be assessed via a food frequency questionnaire (FFQ) and a 3-day food diary before the intervention (between visit 2 and 3).

During the entire run-in and intervention period, the subjects will be asked not to consume any probiotic products other than the study products. During the entire study subjects should maintain their habitual diet and life style such as physical activity level and sleep habits.

**Table 1: Study flow chart**

|                                               | Screening             | Baseline        |                       | Intervention    |                        |
|-----------------------------------------------|------------------------------|------------------------|-----------------------|------------------------|------------------------|
| Assessment                                    | Visit 1
before-3w | Visit 2
-3w | Visit 3
0w | Visit 4
3w  | Visit 5
6w  |
|                                               | Screening             | Baseline 1      | Baseline 2     | Follow-up
1 | Follow-up
2 |
| Screening                                     | x                     |                        |                       |                        |                        |
| Permeability test (urine)                     |                              | x                      | x                     | x                      | x                      |
| Blood sampling                                |                              | x                      | x                     | x                      | x                      |
| Faecal sample collection                      |                              | x                      | x                     | x                      | x                      |
| Cortisol (saliva)                             |                              | x                      | x                     | x                      | x                      |
| IBS symptom scales (GSRS-IBS, IBS-SSS)        |                              | x                      | x                     | x                      | x                      |
| Daily diary - stool frequency and consistency |                              | x                      |                       |                        |                        |
| Quality of life (5Q-5D-5L)                    |                              | x                      | x                     | x                      | x                      |
| Quality of life (QoL-IBS)                     |                              |                        | x                     |                        | x                      |
| Hospital anxiety and depression scale (HADS)  |                              | x                      | x                     | x                      | x                      |
| Perceived stress scale (PSS)                  |                              |                        | x                     |                        | x                      |
| Food Frequency Questionnaire                  |                              | x                      |                       |                        |                        |
| 3-day food diary                              |                              | x                      |                       |                        |                        |
| Compliance diary                              |                              |                        |                       | x                      |                        |
| Adverse events reporting                      |                              |                        |                       | x                      |                        |

## 4.1 Study Period

It is anticipated that the study will start during the first quarter of 2019 and recruitment is anticipated to be complete within 12 months of start.

## 5 Study population

### 5.1 Number of subjects

The sample size is based on the ability to find a significant lactulose/rhamnose ratio difference between one of the probiotic study arms and the placebo arm. A relevant change of 15% in lactulose/rhamnose difference should be detected as significant, which according to the study by Zuhl et al. 2014 amounts to 0.009 points in ratio difference.

The sample size calculation is based on the following assumptions:

- 80% power
- An expected SD of 0.01 (Zuhl et al. 2014)
- Significance (alpha) level of 5%
- Two-sided testing (significance level of 5%)

To account for a potential drop-out rate of 15%, a total of 75 subjects will be randomized (N=25 subjects in each group should be included).

## **5.2 Recruitment**

Patients suffering from IBS and meeting the inclusion criteria (see 5.3) will be recruited during routine visits at the Department of Gastroenterology at the Örebro University Hospital (USÖ) and at the general health centres associated with USÖ, or through information letters sent out by mail and email to patients already diagnosed with IBS. Patients contacted by mail or email will be given the contact details of the investigators or will be asked to send in their contact details so that the investigators can contact them. In addition, advertisement for the study will be distributed at Örebro University in addition to advertisements in the local newspaper and social media. Students at Örebro University will be informed about the study via internal mailing lists, the online education platform 'blackboard' and social media. A webpage will be set up where interested participants can sign up. Interested participants will be invited to a visit at the university or the hospital. During this visit the study staff will inform carefully about the study as well as provide an informed consent form. Participants recruited during the routine visit will also be provided with a written information letter. During the visit the patient will have the opportunity to ask questions. The participants will then be given time to think through a possible participation and will be asked to sign the informed consent. If needed, the participants will be given more time to consider a participation in the study before signing the informed consent. During this time the participant will be given contact information of members of the research group in case any questions arise.

## **5.3 Inclusion and exclusion criteria for IBS-D patients**

### **Inclusion criteria for patients**

1. Signed informed consent
2. Fulfilled Rome IV diagnostic criteria for IBS with predominant diarrhoea
3. Mild-to-severe IBS symptoms according to the IBS severity scoring system (IBS-SSS; a score of  $\geq 75$ )
4. Age: 18-65 years

### **Exclusion criteria for patients**

1. Known organic gastrointestinal disease (e.g. IBD)
2. Previous abdominal surgery which might influence gastrointestinal function, except appendectomy and cholecystectomy
3. History of or present gastrointestinal malignancy or polyposis
4. Recently (within the last 6 months) diagnosed gastrointestinal infection
5. Current diagnosis of dementia, severe depression, major psychiatric disorder, or other incapacity for adequate cooperation

6. Chronic neurological/neurodegenerative diseases (e.g. Parkinson's disease, multiple sclerosis)
7. Autoimmune disease and/or patients receiving immunosuppressive medications
8. Chronic pain syndromes (e.g. fibromyalgia)
9. Chronic fatigue syndrome
10. Severe endometriosis
11. Coeliac disease
12. Recently (within the last 3 months) diagnosed lactose intolerance
13. Females who are pregnant or breast-feeding
14. Regular intake of systemic corticosteroids and anti-inflammatory medication (including NSAIDs) during the last 3 months or incidental use in the last 2 weeks prior to randomisation
15. Recent (< 4 weeks) intake of proton pump inhibitors, PPI (e.g., omeprazol)
16. Use of anti-depressants in the last 3 months
17. Regular oral intake of mast cell stabilising drugs (e.g. sodium cromoglycate) during the last 3 months or incidental use in the last 2 weeks prior to screening
18. Antimicrobial treatment 6 weeks prior to first screening visit
19. Antimicrobial prophylaxis (eg. acne, urinary tract infection)
20. Regular consumption of probiotic products 4 weeks prior to first baseline visit
21. Concurrent or recent (<4 weeks) use of nutritional supplements or herb products affecting intestinal function (e.g. aloe vera, St. John's Wort, fibres, prebiotics) if the investigator considers those could affect the study outcome.
22. Inability to maintain exercise routine and dietary pattern during the study.
23. Abuse of alcohol or drugs
24. Any clinically significant present or past disease/condition which in the investigator's opinion could interfere with the results of the trial

## **6 Methods**

### **6.1 Screening procedures**

#### **Informed consent**

Patients must sign a dated informed consent prior to any trial-related activities. All subjects will be provided with a copy of their own signed and dated informed consent form.

#### **Inclusion and exclusion criteria**

IBS-D diagnosis will be assessed based on the Rome IV criteria by the investigator (Appendix I) and using the IBS-SSS. If not previously performed, tests to exclude other diseases such as IBD or coeliac disease will be ordered, in accordance with the Swedish IBS guidelines. Only IBS-D patients with an IBS-SSS score  $\geq 75$  will be included. Medical history, concomitant illnesses and other background information (including date of birth, sex, body weight and height, education level, diet, current smoking habits, frequency of alcohol consumption) will be collected during a structured interview (Appendix II).

### Dietary intake

Dietary intake will be assessed before and after the intervention by a food frequency questionnaire (FFQ, Appendix III) that has been validated in a Swedish population (Christensen et al. 2013) (Christensen et al. 2014). The questionnaire includes 174 foods and drinks and estimates the dietary pattern during one year. It will take approximately 20 min to complete the questionnaire. In addition, participants will be asked to record their food intake for three consecutive days using a 3-day food diary (Appendix IV).

### 6.2 Case Report Forms (CRF)

For each study participant data from the visits and relative parameters will be recorded on special data collection forms called Case Report Form (CRF). Each CRF must be completed and signed by the investigators to confirm that it has been completed correctly and that it is an accurate representation of the subject's participation in the study.

### 6.3 Investigational product

6475 tablets:  $5 \times 10^8$  CFU *Lactobacillus reuteri* ATCC PTA 6475

Gastrus tablets:  $5 \times 10^8$  CFU *Lactobacillus reuteri* DSM 17938 +  $5 \times 10^8$  CFU *Lactobacillus reuteri* ATCC PTA 6475.

Placebo tablets: Similar in shape and taste to Gastrus tablets but without the *Lactobacillus reuteri* components.

Both study products are delivered in identical containers.

Dosing: One tablet twice a day.

The Study Products shall be kept refrigerated at all times during the study both by the investigators and by the participants. BioGaia AB will provide the Study Products.

### 6.4 Randomisation

Randomisation will be computerised by an independent researcher. A third party not otherwise involved in the study will label the active and placebo study products. Randomisation lists will be kept in sealed envelopes at the study sites and a sealed copy will also be kept at Sponsor site. The envelopes may not be open until all study data have been entered into the database and until the database has been locked. For exceptions, see “Serious Adverse Event” below. Randomisation will be stratified by gender. At screening, subjects will be assigned a screening number starting at 1001, according to their chronological entry into the study. As an example the first subject will have screening number 1001. If the subjects are suitable for study participation, they will receive their randomization number at Visit 1. Randomisation numbers will include the stratification number (Female = 5; Male = 9), and will be allocated sequentially in the order in which the subjects finalise Visit 1. For example, the first female included will receive the randomization number: 5001, whereas the fifth male included will receive the randomisation number: 9005.

Subjects will be asked to return the used packages from the Study Products to allow assessment by the investigator of compliance. The investigators will also assess compliance by a daily checklist distributed to the participants and by interviews at every visit.

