## **11 Adverse events**

Any adverse events and adverse effects will be recorded on the CRF by the investigators. The diagnosis, if available, or each sign or symptom should be recorded. All adverse events observed must be recorded separately. Onset day and resolution day will be recorded for each event.

The investigator will assess each event with regard to its severity:

- Mild: Transient symptoms, no interference with the subject's daily activities.
- Moderate: Marked symptoms, moderate interference with the subject's daily activities but still acceptable.
- Severe: Considerable interference with the subjects daily activities, unacceptable.

The investigator will assess the causality of the FMT for each adverse event in the following manner:

- Unrelated: FMT has not been performed yet.
- Unlikely: The event is most likely related to an aetiology other than the FMT.
- Possible: A causal relationship is conceivable and cannot be dismissed.
- Probable: Good reason and sufficient documentation to assume a causal relationship.

Any pharmacological treatments used for the event will be recorded.

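### Section 6.4 refers emergency unblinding to a section that does not exist, and the only code device described is the whole randomisation list, so breaking one code would reveal more than one allocation.

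*Protocol*

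**What the plan says.** Section 4 describes the trial as a "single-centre, randomised, double-blinded, placebo-controlled intervention study with a parallel design and three study arms". Section 6.4 sets out how the code is held: "Randomisation lists will be kept in sealed envelopes at the study sites and a sealed copy will also be kept at Sponsor site". The rule on access follows directly: "The envelopes may not be open until all study data have been entered into the database and until the database has been locked". The only relief from it is one cross-reference: "For exceptions, see “Serious Adverse Event” below".

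The same section states that "Randomisation will be stratified by gender". It adds that numbers are issued in sequence within each sex (the 5000 series for women, the 9000 series for men) when a participant finalises Visit 1.

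Section 11 is the only later section on safety reporting. It opens with "Any adverse events and adverse effects will be recorded on the CRF by the investigators", then gives severity grades and a causality scale, and ends with "Any pharmacological treatments used for the event will be recorded". Section 12, on data management and statistics, comes next.

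**The concern.** There are two linked problems. First, the exception to the unblinding rule rests entirely on text that is not in the protocol, so site staff facing a serious event would find a prohibition and no procedure. Second, the device described is not built for revealing one participant's arm. An envelope containing a list discloses every allocation on that list.

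Three things are at stake:

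- **Allocation concealment.** Numbers are sequential, so an opened list would also show the arms waiting for participants not yet enrolled or not yet treated.
- **Causality assessment.** Section 11 has the investigator judge each adverse event, and that judgement should be blind to arm.
- **Exploratory symptom and quality-of-life outcomes.** IBS-SSS, GSRS-IBS, HADS and the quality-of-life scales are self-reported and would be open to influence from staff who know the allocation.

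**Working it through.** No power or error-rate calculation applies. The check sets the relevant sections side by side, with simple counts for the size.

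**1. Is there a section to which the cross-reference leads?** The table of contents lists Section 11, Adverse events, and no section on serious adverse events. Section 9 (safety and ethics), Section 10 (withdrawal) and Section 11 contain no definition of a serious event, no reporting rule and no code-break rule. Table 1 has a row for adverse event reporting only. The term used in 6.4 occurs nowhere else in the protocol. The text from 6.4 to Section 12 is continuous, so removed pages do not explain the gap.

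**2. Does Section 11 fit this trial otherwise?** Its causality scale includes "Unrelated: FMT has not been performed yet". FMT is not an intervention here; the arms are two probiotic products and placebo. The section therefore needs correction in any case.

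**3. What would opening an envelope reveal?** Section 6.4 speaks of lists in envelopes. It describes no sealed code for an individual participant and no procedure for releasing a single number. On the mechanism described:

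| Arrangement of lists (not stated) | Planned allocations revealed |
|---|---|
| One list for both sexes | up to 3 × 25 = 75 |
| One list per sex | all of that sex; the split is not given, so more than 1 and fewer than 75 |
| One code per participant (not described) | 1 |

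**4. Would it reveal future allocations?** Section 6.4 issues the randomisation number at Visit 1. Table 1 places Visit 2 at week -3 and Visit 3 at week 0, and Section 4 starts the intervention after Visit 3. Each participant thus holds a number for at least 0 - (-3) = 3 weeks before treatment. Assuming the list is generated in advance, as a computerised list kept under seal would be, opening it partway through recruitment shows the arms of participants still in run-in and of those not yet enrolled.

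**5. Are 75 numbers the limit?** No. Section 10 replaces randomised participants who do not complete. As an illustration, if the 15% drop-out assumed in Section 5.1 occurred among 75, then 0.15 × 75 = 11.25, or about 12 replacements, giving 75 + 12 = 87 numbers. How these would divide between the sexes cannot be known beforehand.

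**The case against.** The strongest reply is that the provable defect is a broken cross-reference and that the rest is inference. Much of this stands.

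- **A reader might infer that unblinding is forbidden outright.** The text does not support that. Section 6.4 expressly foresees exceptions; what is missing is their content.
- **A reader might infer that one opening necessarily exposes the whole trial.** That is not established either. Lists and envelopes are both plural, the content of each is not stated, and randomisation is stratified by sex. Exposure beyond one participant follows from the only mechanism described, but its extent is uncertain. Section 6.4 also names an independent researcher, a separate party who labels the product, and a sealed sponsor copy. Nothing prevents one of them from releasing a single number while site staff stay blind. The protocol does not say that they will.
- **A reader might assume that the same staff see every participant.** The protocol says only that there is one centre, so this premise is not used here.
- **The primary endpoint is a urinary sugar ratio measured by HPLC, and the symptom scales are exploratory and completed by participants.** This is correct and limits the harm. Opening a list at site unblinds staff and does not by itself unblind participants. A narrower route to the primary analysis remains: Section 10 permits discretionary withdrawal, replaces non-completers and names a per-protocol analysis, so knowledge of allocation could affect who is analysed.

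The objection does not remove the central point. Site staff work from the protocol, and it gives them neither the rule nor a means of breaking one code alone.

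**Conclusion.** The point holds in this form: emergency unblinding is foreseen but undefined, and the only code-holding device described would reveal more than the one allocation needed. The upper limit is the whole list (75 planned allocations, more with replacements), or one sex stratum if the lists are separate.

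This rests on two assumptions. One is that no individual code device exists beyond what Section 6.4 describes; if one does, the protocol should say so. The other is that the lists are generated ahead of enrolment.

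The documents do not support a claim that a serious event would inevitably unblind the whole trial or invalidate the primary result. The change is worth making because it is cheap, while an opened list cannot be closed again.

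**What to change.** 1. Reconcile Section 6.4 with Section 11: either write the section to which 6.4 refers or correct the reference. The clinical circumstances that justify a code-break are for the sponsor and investigator to define.
2. Replace the site-held lists with one sealed code per randomisation number, or with release of a single number by the independent third party. Record the date and reason for each release.
3. Prepare spare codes in each sex stratum, because Section 10 replaces non-completers and 75 codes may be too few.
4. Keep the full lists away from site staff until database lock.
5. In the same revision, correct the FMT wording in the causality scale, and the reference in 6.4 to study sites in the plural, since Section 4 describes one centre.

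The cost is a modest set of individual codes (75 plus spares), which the party already labelling the product could prepare, and about one paragraph of protocol text. Sample size, visits and analysis are unchanged.
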